#### Statistical power and sample size considerations for the primary aim

Using the statistical power calculation computer programs designed specifically for MOST studies [64] and accounting for up to 20% attrition, the anticipated sample will afford an 85% statistical power (type I error at two-sided 5%), at an estimated minimal effect size of 0.20 in standard deviation units, what Cohen would consider a “small” effect in behavioral research [65]. The 0.20 minimal effect size represents the smallest main effect that can be supported by the proposed sample size in the MOST intervention components. For illustration, a difference between 20 and 12% abstinence rates, when converted by an arcsine transformation, corresponds to a Cohen’s *d* = 0.22.

*Aim 2. To estimate the cost and incremental cost-effectiveness of evidence-based tobacco treatment components, delivered alone and in combination.*

The base-case cost analysis will take a societal perspective, estimating all costs associated with treatment components delivered separately and in combination. We will conduct a separate cost analysis from the provider’s perspective. We will use standard methods [66] of incremental cost-effectiveness analysis to estimate the additional cost per quit achieved, where cost includes both intervention costs and 6-month downstream costs of related health care tobacco cessation services, and the effectiveness measure is defined by 7-day point prevalence abstinence at 6 months.

Given the primary focus of the trial on non-economic endpoints, and sample size requirements associated with these endpoints, formal hypothesis testing on the economic outcomes will not be conducted. Resource utilization and cost data are typically skewed, and therefore, the sample size of the trial may be insufficient to detect significant differences in costs between study arms [67]. The economic impact of the intervention will be evaluated using standard incremental cost-effectiveness analysis methods. For example, it is possible that several treatment combinations may yield comparable effectiveness in abstinence. If this happens, then the incremental cost per abstinence may be factored into this consideration. Sensitivity analysis will be conducted to assess the impact of assumptions and uncertainty on results and conclusions [66, 68]. This analytic approach is appropriate in economic studies that “piggyback” randomized trials [69].

*Aim 3. To conduct a robust, mixed methods evaluation of the implementation process and assess site characteristics and organizational factors that may influence the implementation of tobacco treatment in lung cancer screening settings.*

Descriptive statistics will be used to summarize key implementation outcomes (reach, adoption, fidelity, acceptability, appropriateness) collected from SC surveys [25]. Site characteristics will also be used in exploratory analyses on variation in cessation and implementation outcomes to examine the extent to which site characteristics are associated with intervention effectiveness, fidelity, and acceptability. To better understand the implementation challenges and sustainability, semi-structured interviews with SCs will be conducted following the completion of study participation. Interviews will be audio-recorded and transcribed. Led by an experienced qualitative methods specialist (QMS), a team of trained and supervised coders will analyze the transcripts using NVivo Pro version 12.0, a qualitative data analysis management software program [70]. Coders will utilize a thematic text analysis approach, which will occur in two phases [60, 71, 72]. In the first phase, the team will iteratively develop a codebook based on a priori domains and inductive concepts that emerge from the data, meeting regularly to reach a consensus on code name and definition. Then, all transcripts will be independently coded, and the QMS will complete a quality assurance check of the dataset. In the second phase, the team will group coded statements into analytic domains, and review these categories to identify and describe major and minor thematic areas. Themes will include sentiments that appear across most transcripts, as well as any significant divergences.

*Aim 4: To analyze whether lung cancer screening results (i.e., Lung-RADS) moderate smoking abstinence outcomes.*

We will use the Lung-RADS category score (1–4) as an ordinal measure of lung cancer screening findings and examine whether the proportion of participants achieving smoking abstinence differs by the degree of screening abnormalities (Lung-RADS score).

For the PACT ancillary study, interview transcripts with the SCs and PACT participants will be coded utilizing a grounded theory approach, consisting of open, axial, and selective coding phases [73]. Analytic software NVivo Pro v. 12.0 will be used to facilitate the analysis [70]. Using the grounded theory approach, two coders will independently code each transcript with the goal of identifying and describing themes that persistently emerge as barriers to recruitment to CASTL, meeting regularly to reach a consensus on code names, definition, and assignment to content. Each phase of analysis will be used to iteratively generate a theory to inform reasons for tobacco treatment trial refusal among Black participants.

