**Methods:**

The Cessation and Screening to Save Lives (CASTL) trial seeks to advance knowledge about the reach, effectiveness, and implementation of tobacco treatment in lung cancer screening. We describe the rationale, design, evaluation plan, and interventions tested in this multiphase optimization strategy trial (MOST). A total of 1152 screening-eligible current smokers are being recruited from 18 LCS sites (*n* = 64/site) in both academic and community settings across the USA. Participants receive enhanced standard care (cessation advice and referral to the national Quitline) and are randomized to receive additional tobacco treatment components (motivational counseling, nicotine replacement patches/lozenges, message framing). The primary outcome is biochemically validated, abstinence at 6 months follow-up. Secondary outcomes are self-reported smoking abstinence, quit attempts, and smoking reduction at 3 and 6 months. Guided by the Implementation Outcomes Framework (IOF), our evaluation includes measurement of implementation processes (reach, fidelity, acceptability, appropriateness, sustainability, and cost).

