### Study setting and site recruitment

This trial is being conducted at 17 LDCT-LCS sites across the USA. Recruitment of participating sites and site coordinators (SC) was led by the staff from the GO2 Foundation for Lung Cancer (GO2) (formerly Lung Cancer Alliance). Sites were eligible for participation in the CASTL trial if they were part of GO2’s Screening Centers of Excellence (SCOE) national network indicating having met several criteria for high-quality screening practices. Study sites were required to have at least 1 year of lung cancer screening experience, employ at least one SC, and report conducting at least 20 LDCT screenings per month so as to have an adequate patient volume for achieving the target recruitment of patients who smoke during the allotted study time frame. To promote participant diversity, there was attention paid to selecting a wide variety of LDCT-LCS sites both with and without academic affiliations and with geographic diversity across the USA. LDCT-LCS sites were recruited and onboarded in staggered waves.

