### Participant recruitment

Each site has a target enrollment of 64 participants (total *n* = 1152). All participants who report current smoking are identified by the SCs (or designee) who introduce the CASTL study to all eligible patients during scheduling for their LDCT scan. SCs provide names and contact information of interested patients to the Memorial Sloan Kettering Cancer Center (MSK) study staff daily. SCs also maintain a detailed screening log of all people reporting current smoking with LDCT-LCS appointments and provide weekly de-identified updates regarding the number of people currently smoking who were ineligible for CASTL and the reasons for ineligibility. Information reported includes the number of refusers, their reasons for refusal, and limited demographic characteristics (age, gender, race, and ethnicity) of all people who currently smoke seeking LDCT-LCS. These screening logs provide the information needed to determine the reach rate, the proportion of eligible, participants who enroll in the CASTL trial.

An MSK Clinical Research Coordinator (CRC) emails potential participants a study introduction letter shortly after interested participants are referred by the SCs and makes up to 3 telephone attempts to confirm their eligibility. Trained CRCs have a non-written (verbal) informed consent discussion with participants so as to confirm eligibility prior to randomization. Participants will receive study information by mail following these consent discussions. Initially, consent was obtained prior to their lung cancer screening visit, or within seven business days of the completion of their LDCT scan. However, the COVID-19 pandemic issues resulted in LDCT-LCS sites reporting closures, scheduling delays, and disruptions requiring a protocol amendment to allow for enrollment of eligible patients anytime in LDCT clinical workflow between 60 business days prior to the LDCT appointment and 60 business days following the scan.

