## Trial status and modifications

Protocol version: A(13) Approved 03/03/2022.

Patient enrollment began in August 2018 and is ongoing (currently enrolled: *n* = 734). We anticipate completing recruitment in Fall 2022 and data collection in Spring 2023, after which analysis will begin. The COVID-19 pandemic had a marked impact on participant recruitment resulting from site closures and redeployment of screening site staff. The research team has made several modifications designed to expand recruitment timelines in order to help reduce staff burden and facilitate study implementation across the sites. These included (1) increasing recruitment timelines from 7 business days post LDCT scan to a period of 120 business days (60 pre/60 post) LDCT scan to allow site coordinators to look forward or backward on their schedules, (2) allowing the study PIs and staff to deliver interventions if needed, (3) reducing the age and smoking history requirements to match the updated USPSTF guidelines for screening, and (4) providing additional incentive for the timely return of saliva samples. All of these changes were approved by the IRB prior to implementation. Due to the continued disruptive impact of COVID-19, we have opted to not open our 18th screening site to recruitment. We have also decided to close some non-performing sites. As a result of these pragmatic decisions, we will not be able to achieve the initially planned 1152 participants for this study.

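### The 85% power at 0.20 SD belongs to about 1123 to 1152 randomised, a number the article itself says will not be reached, and the power statement was not revised

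*Protocol article*

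**What the plan says.** The section on statistical power for the primary aim states that "the anticipated sample will afford an 85% statistical power (type I error at two-sided 5%), at an estimated minimal effect size of 0.20" SD, after "accounting for up to 20% attrition". It adds that "The 0.20 minimal effect size represents the smallest main effect that can be supported by the proposed sample size", and illustrates the scale with the remark that "a difference between 20 and 12% abstinence rates, when converted by an arcsine transformation, corresponds to a Cohen’s *d* = 0.22".

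That section prints no sample size beside the power figure. The only planned total in the article is 1152. The abstract says "A total of 1152 screening-eligible current smokers are being recruited from 18 LCS sites", the study design overview repeats 18 sites and 1152, and the participant recruitment section says "Each site has a target enrollment of 64 participants (total *n* = 1152").

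Two other sections have moved on. The study setting section says "This trial is being conducted at 17 LDCT-LCS sites across the USA". The trial status section reports 734 enrolled with recruitment ongoing, an 18th site that will not be opened and some non-performing sites being closed, and concludes that "we will not be able to achieve the initially planned 1152 participants for this study". Neither it nor the power section gives a revised sample size, power or detectable effect.

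**The concern.** The power statement is in the present and future tense and refers to the sample that is anticipated. The trial status section is current information, not a log of superseded text, and it says the planned sample will not be obtained. If the 85% belongs to the abandoned number, the article claims sensitivity that the trial will not have on the same inputs.

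This matters because the main deliverable is an optimised package, and the analysis section selects model terms largely by statistical significance. At the stated 85%, a true main effect of 0.20 SD would be missed 15% of the time. At 734 randomised with 20% loss, it would be missed about 32% of the time. A reader weighing a non-significant component needs to know where between these figures the trial stands.

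**Working it through.** **Inputs.** From the power section: main effect d = 0.20, two-sided 5%, attrition up to 20% (taken at 20%), power 85%. From Table 1: each component level covers 8 of the 16 conditions, so with equal cell sizes (assumed) a main effect compares half the sample with the other half. From the trial status section: 734 enrolled, taken here as 734 randomised.

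**Formulas.** For n analysed in two equal halves, the standard error of d is 2/√n. Hence power = Φ(d√n/2 − 1.96), and the effect detectable with 85% power is 2(1.96 + 1.036)/√n.

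**Reproducing the plan's figure.** n = 0.8 × 1152 = 921.6. Then 0.20 × √921.6 / 2 = 3.036, and Φ(3.036 − 1.96) = Φ(1.076) = 85.9%. A noncentral t version gives 85.8%. In reverse, 85% needs n = (2 × 2.996 / 0.20)² ≈ 898 analysed, which is 898/0.8 ≈ 1123 randomised. Without attrition, 1152 would give 92.4%, so the printed 85% is the figure for 1152 less 20%. The arcsine illustration also checks: 2·arcsin√0.20 − 2·arcsin√0.12 = 0.220.

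**Same inputs at smaller totals.** Seventeen sites at 64 each give 17 × 64 = 1088, the ceiling if no site exceeds its target. The 734 already enrolled are the floor.

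| Randomised | Analysed (−20%) | Power at 0.20 SD | Effect detectable with 85% power |
|---|---|---|---|
| 1152 | 921.6 | 85.9% | 0.197 SD |
| 1088 | 870.4 | 83.9% | 0.203 SD |
| 1000 | 800 | 80.7% | 0.212 SD |
| 900 | 720 | 76.5% | 0.223 SD |
| 800 | 640 | 71.6% | 0.237 SD |
| 734 | 587.2 | 67.8% | 0.247 SD |

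Starting from 12% abstinence on the arcsine scale, 0.197 SD corresponds to about 19% and 0.247 SD to about 21%. For the article's own illustration of 20% against 12%, a two-proportion formula with 20% attrition gives about 91% at 1152 and about 75% at 734.

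**Alternative reading of attrition.** The analysis section counts participants with missing outcomes as non-abstinent, so nobody leaves the denominator. If 0.20 SD is assumed to be the effect on that scale, no attrition discount is needed: 898 randomised gives 85%, and 734 gives Φ(0.20 × √734 / 2 − 1.96) = Φ(0.749) = 77.3%.

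All figures use an unadjusted two-sided 5%, as the power section does. The false discovery rate adjustment in the analysis section would lower power further; that is not quantified here.

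**The case against.** The strongest reply is that there is no calculation error. The 85% reproduces and so does the arcsine illustration. What remains is a design-stage statement that was not refreshed, in an article that openly reports the shortfall; the per-site and total figures can be read as targets. All of this stands, but disclosing the smaller number is not the same as disclosing its consequence. The power sentence speaks of what the anticipated sample will afford, and on its stated inputs that cannot be a sample of 1088 or fewer.

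Second, the size of the loss is not established. Recruitment was continuing, so 734 is an interim count, and at 1088 the gap from 85% is only about 1 point. This stands, and it limits the conclusion to a range.

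Third, 85% is not tied to exactly 1152. About 1123 suffices at 20% loss. The article says up to 20%, and 1000 randomised with 10% loss would leave 900 analysed and also give 85%. With missing counted as non-abstinent and 0.20 SD already on that scale, about 898 randomised is enough. This stands as a possibility. However, the power section says it allows for attrition, and if 0.20 SD is instead an effect among completers, counting missing as non-abstinent would normally shrink it, which makes the discount reasonable. The article does not say which is meant.

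**Conclusion.** The point holds as an inconsistency between the power section and the trial status section. With 20% attrition, the 85% at 0.20 SD corresponds to about 1123 to 1152 randomised, and the article says 1152 will not be reached. On the same inputs, power lies between 67.8% (734, the floor) and 83.9% (1088, the ceiling if no site exceeds its target). The overstatement is therefore about 1 to 17 points, and the effect detectable with 85% power is about 0.203 to 0.247 SD instead of 0.197 SD. These figures assume equal cell sizes, 20% loss and an unadjusted 5% level.

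A reader might infer that the trial's power is 68%, or that 85% is certainly lost. The documents support neither. The final number is not stated, 734 is not the final count, and 85% survives at about 898 randomised if 0.20 SD already allows for missing counted as non-abstinent. Nor does the finding mean that the original sample size calculation was wrong.

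**What to change.** In the power section, replace the 85% and 0.20 SD statement with power and minimal detectable effect at the expected final number randomised. If that number cannot yet be given, print a short table from 734 to 1088 like the one above. State whether 0.20 SD is the effect with missing outcomes counted as non-abstinent or the effect among those followed up, and apply or omit the 20% discount accordingly. In the abstract, the study design overview and the participant recruitment section, label 1152 and 18 sites as the initial target and bring the current numbers into line with the trial status section.

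This is a change of wording only. It needs no extra participants and alters no endpoint, allocation or primary model. The cost is a less favourable stated power.

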### Data management and monitoring

A multidisciplinary study team was assembled to lead and manage the day-to-day responsibilities of this study. This team includes MPIs from MSK—the study sponsor and data coordinating center—and New York University, study staff based at MSK including co-investigators, a project manager, CRCs, and regulatory support staff who will be responsible for the day-to-day management of the study and research staff at the GO2 will work in partnership with the CASTL study team to identify and recruit participating screening sites. The core study team—the MPIs, MSK study staff, and GO2 staff—will meet bi-weekly to oversee study conduct and overall progress. Additional team members will include consultants from multiple institutions^1^ around the country and screening site staff—a site PI and site coordinator. Site coordinators will be responsible for referring potential participants to the study and providing study interventions. Bi-weekly meetings will be conducted with site coordinators, the MPIs, MSK study team, and GO2 representatives for supervision intended to promote adherence to the study protocol and provide ongoing support to the SCs.

The survey data collected is managed via the study’s REDCap database by the RPA, CRC(s), and Clinical Research Supervisor [74]. To ensure confidentiality of data, all records, including hard copies of study documents, will be identified using the participant’s unique study identifier, not by name, and will be stored in a locked secure area at MSK. Only the PI and MSK research staff will have access to the study files and REDCap records. Recorded site coordinator interviews will be uploaded to a secured shared drive at MSK. Biospecimens (saliva samples) collected for the bio-verification of abstinence will be assigned a unique identifier and stored at an MSK laboratory. Any portion of the sample remaining after testing is completed will be discarded and will not be stored for use in future ancillary studies. Although this is a minimal risk trial, it is monitored by the MSK Data Safety and Monitoring Board (DSMB), which is composed of a plurality of voting members who are not affiliated with MSK. Random-sample data quality and protocol compliance audits will be conducted by the study team, at a minimum of two times per year, more frequently if indicated.

Protocol amendments will be managed by the study team at MSK, the IRB of record. Participating sites will be notified of amendments and copies of revised protocol will be shared with sites for addition to their regulatory binders. Any deviations from the protocol, adverse events (AEs), and/or serious adverse events (SAEs) will be reported to the PIs and submitted to MSK’s IRB for review.

### Criteria for removal and adverse events

We do not anticipate any serious adverse events that are detrimental to study participants to occur as this is a minimal-risk trial. In the unlikely event that a participant expresses distress, the research staff will refer to appropriate assistance at each site as needed, or to the study PIs if appropriate. It will be made clear to all study participants (SCs and smokers) that they are allowed to withdraw from the study at any time or discontinue the use of the medication if they experience serious adverse reactions. Participants will be asked if they would like their data to be excluded from the trial at the time of withdrawal as long as that data has not already been otherwise used or shared. These requests must be received in writing. Participants are informed that there is no anticipated harm or compensation for post-trial participation beyond incentives for survey completion. If at any time the participant is found to be ineligible for the protocol (e.g., they are ineligible for lung cancer screening or a contraindication with combination NRT is discovered post-randomization) as designated in the section on criteria for patient/subject eligibility, the participant will be removed from the study. We will also remove patients who do not complete the baseline assessment from the study. Allocated interventions will not be otherwise discontinued or modified.

### Data sharing and dissemination plan

Participants will be asked for permission for the research team to share relevant data with study collaborators and regulatory bodies such as the NCI. Requests made by other researchers for the study protocol and/or data will be considered by the study sponsor. For annual data transfers to the NCI, de-identified data will be shared through a secure online portal managed by the NCI in accordance with the data transfer agreement for analysis and use in related collaborative projects. The datasets analyzed during the current study and statistical code are available from the corresponding author on reasonable request, as is the full protocol. Any shared data will be de-identified.

Study findings will be disseminated primarily through peer-reviewed manuscripts and presentations at relevant scientific conferences. Findings will also be disseminated by collaborating colleagues from the National Cancer Institute, the GO2 Foundation, and the National Lung Cancer Roundtable.

